# Stimulation of the Tibial nerve Repetitively to Improve Incontinence in Parkinson’s Electronically (STRIPE trial): a randomised control trial of tibial nerve stimulation for bladder symptoms in Parkinson’s disease using a self-contained wearable device

**DOI:** 10.1186/s13063-022-06827-3

**Published:** 2022-10-28

**Keywords:** Bladder symptoms, Parkinson’s disease, Neuromodulation, Tibial nerve stimulation, Randomised control trial

## Abstract

**Background:**

Bladder symptoms are common in Parkinson’s disease (PD), affecting half of all individuals. These have significant impact on quality of life as well as implications for morbidity, contributing to falls and hospital admission. The treatment of bladder symptoms can be complicated by the tendency to side-effects in people with PD including cognitive impairment and gait instability with anti-muscarinics. The development of new, better treatments is therefore warranted. Tibial nerve stimulation is a form of neuromodulation demonstrated to improve overactive bladder symptoms in non-neurogenic cohorts. Previously requiring hospital attendance, we aim to explore the use of this intervention using a simple device that can be used by patients at home.

**Methods:**

STRIPE is a phase II randomised control trial of tibial nerve stimulation delivered by the Geko™ device, a small, self-adhesive neuromuscular stimulation device currently used for thromboembolism prophylaxis post-surgery. Active tibial nerve stimulation will be compared to sham stimulation, with participants blinded to treatment allocation and undertaking outcome assessment whilst still blinded. Participants will be asked to self-administer stimulation at home twice per week, for 30 min per session, over the course of 3 months. Primary outcome measure will be the International Consultation on Incontinence Overactive Bladder Questionnaire (OAB) at week 12. Secondary outcomes will include pre- and post-intervention bladder diary (frequency, urgency episodes, nocturia), patient perception of global change, bowel function and bladder-related quality of life. Participants will be recruited from the Proactive Integrated Management and Empowerment (PRIME) cross-sectional trial in which participants have been screened for bladder symptoms and invited to take part, as well as clinician referral from around the region.

**Discussion:**

This trial will involve a randomised control trial of a novel and easy to use method of delivering tibial nerve stimulation for PD in the patient’s own home. This may potentially have huge benefit, avoiding the problems with side effects that can be seen with anti-muscarinics and providing a new potential modality of treatment.

**Trial registration:**

ISRCTN11484954. Registered on 22 June 2021.

## Introduction

### Background and rationale {6a}

Parkinson’s disease is the second most common neurodegenerative disorder, affecting one in 37 people during their lifetime [1]. A recent large-scale study suggests up to 57% of individuals with Parkinson’s (PD) report bladder symptoms [2]. These have a profoundly negative impact on quality of life [3] and have been identified as a priority area for research by people with PD [4]. Continence concerns can affect confidence with mobility and independence, such as ability to leave the house, and nocturia affects sleep. The impact of urinary symptoms is worsened by the movement disorder, with people unable to act quickly on urgency episodes contributing to incontinence, and nocturia being problematic due to PD medication being less effective at night. Urinary symptoms are strongly implicated in causing falls and contribute to the risk of hospitalisation [5], with consequent costs to the health system and wider society.

Anti-cholinergic drugs are utilised most commonly but are poorly tolerated despite evidence of their effectiveness. These cause dry-mouth and constipation (negatively impacting dopaminergic drug absorption), precipitate cognitive impairment and can precipitate falls through exaggeration of gait dysfunction [6].

Recently beta-3 agonists have been developed which do not have cognitive side effects, but their benefit can be modest and worsen supine hypertension—another non-motor feature of PD [7]. Bladder botulinum toxin injections are a relatively recent development in the field and, although not generally associated with systemic effects, are resource-intensive and require a population with mobility problems to frequently attend hospital. New approaches to treatment are therefore a high priority if they can overcome the limitations inherent in current therapies.

#### Neuromodulation for bladder symptoms

Neuromodulation has arisen as a method of controlling bladder symptoms by indirectly modulating the nerve supply that controls the bladder. Aside from implantable sacral nerve root stimulators, one method for delivering this is percutaneous tibial nerve stimulation (PTNS). This involves the application of pulsed stimulation to the tibial nerve at the level of the medial malleolus using needle electrodes. This is performed in the urology clinic requiring the patient to attend a course of treatments over several weeks. This can lead to a significant improvement in idiopathic overactive bladder symptoms [8]. The mechanism of action is unclear but may involve modulation of aberrant spinal reflexes [9]. Three studies have demonstrated efficacy of PTNS in populations with PD, with two studies proving significant improvements in urodynamic parameters [10–12]. The advantage of this approach is that it avoids the systemic and cognitive effects that are limiting factors when using pharmacological therapy.

A further evolution of PTNS has been to deliver neuromodulation via the tibial nerve transcutaneously (transcutaneous tibial nerve stimulation—TTNS). This allows non-invasive treatment in the home environment, overcoming situations where use of PTNS in PD may be limited by mobility and burden of attending hospital regularly. TTNS has been shown to be non-inferior to PTNS [13] and has been used successfully in conditions such as multiple sclerosis [14]. Preliminary studies suggest TTNS may be beneficial and well tolerated in individuals with PD [15–17], but are limited currently with regard to sample size and comparison to sham therapy. The majority of current studies exploring TTNS have utilised TENS machines (trancutaneous electrical nerve stimulation). Whilst capable of delivering effective non-invasive stimulation, these devices are complex and unwieldly. They require multiple wires to be attached and electrodes placed accurately to achieve stimulation of a specific nerve. The pulse generator units tend to be designed to provide a range of settings and often feature many buttons, dials or touch screen interfaces. This poses a significant practical difficulty for individuals who invariably have mobility or dexterity problems, as well as potential cognitive impairment.

#### Rationale for study

The importanceof bladder symptoms in individuals with Parkinson’s is evident from the scientific literature and priorities reported by patients [4]. Challenges are posed by limited tolerability and modest efficacy of current treatments. We intend to recruit participants to take part in a randomised control trial (RCT) of TTNS delivered by the Geko™ device. This is a simple self-contained device which can be easily adhered to the ankle with many advantages over the use of a TENS device which include ease of use and lack of trailing wires as a safety consideration. A pilot study has been previously performed by different authors supporting the feasibility of using the Geko™ device for treating bladder symptoms [18], assessed in a cohort with idiopathic overactive bladder and multiple sclerosis.

### Objectives {7}

#### Hypotheses

Tibial nerve stimulation using the Geko™ device will improve bladder symptoms in people with Parkinson’s disease as compared to sham (placebo) stimulation.

#### Primary objective

To assess the effect of transcutaneous tibial nerve stimulation delivered by the Geko*™* device versus sham stimulation in people with PD and bladder symptoms on the International Consultation on Incontinence Questionnaire overactive bladder (ICIQ-OAB) score.

#### Secondary objectives

To assess the effect of Geko*™* device delivered tibial nerve stimulation versus sham stimulation in people with PD with bladder symptoms on:Total number of incontinence episodes and extent of nocturiaBowel functionDepressionQuality of lifeNon-invasive urodynamic parameters

### Trial design {8}

This study has been designed to be a phase II, randomised control trial with two arms: active stimulation at the tibial nerve and sham stimulation (allocation ratio 1:1) lasting 24 weeks. Participants will be blinded as to treatment allocation and assessment performed by participants whilst blinded. The aim of the study is to demonstrate superiority of active stimulation over sham. Figure 1 demonstrates the trial design in a flow chart format.

**Fig. 1 Fig1:**
[figure not shown]
Flow chart demonstrating trial design

## Methods: participants, interventions and outcomes

### Study setting {9}

We aim to recruit 220 individuals with idiopathic Parkinson’s disease (PD) who have symptoms of urgency, nocturia or both in combination. Participants will be recruited from several sources; the PRIME-Parkinson cross-sectional study (IRAS 285,401) comprises a large sample of patients with parkinsonism across the Bath, West Wiltshire and North-East Somerset region, through advertising via research databases and via referral from appropriate clinicians throughout the UK.

In-person assessment will be carried out at the point of enrolment for baseline assessment and device training, and follow-up undertaken virtually (telephone/video call) after the intervention period for final assessment. The device will be applied and utilised by patients in their own homes between assessment visits. In person, assessments will be carried out through the Research Institute for Care of the Older Person (RICE), Bath, UK. Ongoing support whilst taking part in the trial will be provided by the team at the University of Bristol.

### Eligibility criteria {10}

#### Inclusion criteria

Diagnosis of idiopathic Parkinson’s diseasePresence of overactive bladder symptomsAble to give informed consent

#### Exclusion criteria

Cognitive impairment to the extent of being unable to engage in assessmentsAbnormality of both lower limbs precluding device placement on at least one ankle, including recent surgery to this regionPacemaker, implanted defibrillator, sacral nerve stimulator or deep brain stimulatorLimited life expectancy in final palliative stages of conditionAlternative cause of parkinsonism including but not limited to drug-induced parkinsonism, progressive supranuclear palsy, multiple system atrophy, corticobasal degeneration and vascular parkinsonismBladder treatment medication including anti-muscarinic, beta-3 agonist, alpha-blocker, 5-alpha reductase inhibitor commenced in the 3 months prior to enrolment, or dose change within last 3 monthsRecently diagnosed deep vein thrombosis—within the last 3 monthsProven urinary tract infection—within the last 1 month (new onset lower urinary tract symptoms or non-specific illness coupled with established microbial growth on a mid-stream urine specimen)Current treatment for urological cancer excluding prostate cancer (unless judged suitable at the CI’s discretion)Severe benign prostatic hypertrophy, based on history of predominant voiding symptomsBladder botulinum toxin injections, percutaneous tibial nerve stimulation or previous sacral nerve stimulation in the year prior to enrolmentSevere nocturnal polyuria (Nocturnal Polyuria index > 50%) in cases of isolated nocturia without urgencyPost void residual > 300 ml or residual > 100 ml with symptomatic history for incomplete bladder emptyingThe inclusion of ‘overactive bladder symptoms’ was operationalised as patient-reported symptoms of urgency or frequency without a significant post-void residual volume demonstrated on ultrasound scan as above

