#### Relevant concomitant care permitted or prohibited during the trial {11d}

Pre-existing medications for bladder symptoms and other relevant treatments that may have any influence on bladder function can be continued during the trial period, as long as they are stable without dosing changes. All medications taken by a participant will be recorded in their case record file and any changes made during the period of the study confirmed. Commencing a new relevant medication within the three previous months is a criterion for exclusion but will not preclude recruitment once the 3-month timepoint is reached.

For participants who have been introduced through specialist urology services and are currently considering a specialist treatment such as bladder botulinum toxin, sacral nerve stimulation or catheterisation, recruitment into the study will be dependent on the patient agreeing that this is suspended until completion of the intervention period.

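### The one-year neuromodulation exclusion names percutaneous but not transcutaneous tibial nerve stimulation, so current or recent users of the modality under test meet no exclusion

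*Protocol article*

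**What the plan says.** All references are to the protocol article.

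- **Exclusion criteria (under Eligibility criteria {10}).** The one-year exclusion covers bladder "botulinum toxin injections, percutaneous tibial nerve stimulation or previous sacral nerve stimulation in the year prior" to enrolment. TTNS is not named. The device criterion lists a pacemaker, implanted defibrillator, sacral nerve stimulator and deep brain stimulator. The three-month rule concerns bladder medication.
- **Neuromodulation for bladder symptoms.** The percutaneous form (PTNS) is described as "pulsed stimulation to the tibial nerve at the level of the medial malleolus using needle electrodes", given in a urology clinic. The next step is to "deliver neuromodulation via the tibial nerve transcutaneously (transcutaneous tibial nerve stimulation—TTNS"), which is non-invasive, can be done at home and has mostly been delivered by TENS machines. The section adds that "TTNS has been shown to be non-inferior to PTNS".
- **Rationale for study.** The trial is a "randomised control trial (RCT) of TTNS delivered by the Geko™ device".
- **Relevant concomitant care permitted or prohibited during the trial {11d}.** The rule on continuing treatment reads: "Pre-existing medications for bladder symptoms and other relevant treatments that may have any influence on bladder function can be continued during the trial period". A condition is attached, namely that this holds "as long as they are stable without dosing changes". A separate paragraph deals with patients introduced through urology services who are considering a specialist treatment. It gives botulinum toxin, sacral nerve stimulation and catheterisation as examples of what would be suspended until the intervention period ends.

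**The concern.** The exclusion removes people whose bladder symptoms have recently been treated by stimulating the tibial nerve through a needle. It leaves in people who have had the same nerve stimulated through the skin, which is what the trial tests. The article reports the two forms as non-inferior, so whatever reason supports excluding recent PTNS applies equally to TTNS.

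What is at stake is the size of the contrast. A sham participant with their own TTNS would be receiving tibial stimulation outside the trial, and an active participant with their own TTNS may have less to gain from the study device. Both pull the active-sham difference towards zero. The article itself takes care to keep tibial stimulation out of the sham arm: the sham site and setting were chosen for that purpose, and the Discussion stresses it. An eligibility rule that admits users of TTNS sits badly with that aim.

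**Working it through.** **Step 1: does the text cover TTNS anywhere?**

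| Provision | Reaches a TTNS user? |
|---|---|
| One-year exclusion (botulinum toxin, PTNS, sacral stimulation) | No. The article defines PTNS by needle electrodes and TTNS as a different, transcutaneous form. |
| Device exclusion | No. It names cardiac devices and sacral and deep brain stimulators, not an external unit. |
| Three-month stability rule | No. It concerns bladder medication. |
| Suspension paragraph in {11d} | Not clearly. It addresses urology patients considering a specialist treatment, not people already using TTNS. |
| Continuation sentence in {11d} | Arguably lets stable TTNS continue, under its reference to other relevant treatments. |

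No exclusion applies. Minimisation (Sequence generation {16a}) uses age category and current bladder medication, so neuromodulation use is not balanced by design, although randomisation balances it in expectation.

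**Step 2: reproduce the planned sample size.** Inputs from Sample size {14}: SD 2.5, difference 1 point, two-sided 0.05, power 80%, attrition 10%. The 1:1 allocation is from Trial design {8}.

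- n per arm = 2 × (1.96 + 0.8416)² × 2.5² / 1² = 2 × 7.849 × 6.25 = 98.1, rounded up to 99.
- With 10% attrition: 99 / 0.9 = 110 per arm, 220 in total. This matches the plan.

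**Step 3: worst-case dilution.** Let f be the share of each arm using TTNS. The article does not give f, so a range is assumed. Suppose users have no remaining active-sham difference. The expected difference is then (1 − f) × 1 point.

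- SE = 2.5 × √(2/99) = 0.355.
- Power = Φ((1 − f)/SE − 1.96).

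| f (assumed) | Users among 220 | Difference | Power | Loss (percentage points) |
|---|---|---|---|---|
| 0 | 0 | 1.00 | 80.4% | – |
| 1% | about 2 | 0.99 | 79.6% | 0.8 |
| 2% | about 4 | 0.98 | 78.8% | 1.6 |
| 5% | 11 | 0.95 | 76.2% | 4.2 |
| 10% | 22 | 0.90 | 71.7% | 8.7 |

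The loss is negligible at 1% to 2% and becomes material only at prevalences that nothing in the article supports.

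**The case against.** **Use is probably rare.** The article calls the Parkinson's evidence for TTNS preliminary, describes TENS devices as impractical for people with dexterity problems, and describes the Geko device's UK approval as being for thrombosis prevention. Nothing shows established home TTNS in the source population. This stands, and it is why the low end of the range matters most.

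**The dilution model is a worst case.** The Discussion notes that the device's 1 Hz departs from the 10–20 Hz common elsewhere, so a person's own TENS is not the tested regimen. Every entrant must also still have overactive bladder symptoms. Some active-sham difference may therefore remain in users. This stands too.

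**The article condenses a fuller protocol (version 3.0).** That document may define the permitted treatments. However, the article prints an itemised exclusion list that names the neighbouring modality, so the gap lies in a stated rule. If the full protocol already covers TTNS, that is quickly confirmed.

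A reader might also infer several stronger things that the article does not support:

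- *That {11d} expressly lets sham participants keep using TTNS.* The continuation sentence opens with medications, requires no dosing changes and is followed by sentences about medication. Ongoing TTNS is a possible reading, not a stated permission.
- *That leaving TTNS out of the suspension paragraph permits it.* The treatments there are introduced as examples, and the paragraph concerns patients considering a specialist treatment.
- *That the eligibility and concomitant-care sections contradict each other.* They do not. One leaves a gap that the other does not close.
- *That the omission is what threatens blinding.* Someone who has learnt the medial ankle site may recognise the sham, but that knowledge does not lapse after a year. People with older PTNS experience are admitted already, and a one-year TTNS exclusion would not change this.
- *That carry-over favours one arm.* Under 1:1 randomisation recent users are expected to balance, so the consequence is dilution or noise rather than a spurious benefit.

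**Conclusion.** The point holds as a gap in wording. The one-year exclusion omits the modality under test, no other criterion reaches it, and the rule followed exactly admits current or recent TTNS users to either arm. The direction of the effect is towards no difference.

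The size is unknown because the prevalence of use is not given, and it is probably small: under the worst-case assumption, about 1 to 2 percentage points of power at 1% to 2% use, and about 4 to 9 points at 5% to 10%. These figures rest on equal use in both arms, no remaining active-sham difference in users, SD 2.5 and 99 evaluable per arm. The textual gap does not depend on them. The planned sample size reproduces and need not change. Priority: minor.

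**What to change.** 1. In the exclusion criteria, extend the tibial item to percutaneous or transcutaneous tibial nerve stimulation in the year before enrolment, and mention TENS at the ankle so that screeners recognise it.
2. Add one question on prior and current TTNS or ankle TENS use at the screening contact, and record the answer. For participants already enrolled, collect the same information so that the extent of use is known.
3. Reconcile the concomitant-care wording on other relevant treatments with the extended criterion. What may or may not continue during the trial is for the sponsor to decide. The request is only that the two sections can be read together without doubt.

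The cost is a phrase in the exclusion list, a clarification in {11d} and one screening question. The downside is the loss of a small number of candidates.

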### Who will take informed consent? {26a}

Written consent will be obtained for all participants by members of the research team trained in Good Clinical Practice. Verbal consent over the telephone will be obtained to collect bladder diary data prior to formal enrolment which will be used to help determine eligibility. This is intended to avoid potential participants, who are subsequently found to be unsuitable/ineligible, attending for an unnecessary in-person visit. Individuals without the capacity to make a decision to take part will not be eligible for inclusion.

### Additional consent provisions for collection and use of participant data and biological specimens {26b}

An ancillary qualitative study assessing the impact of bladder symptoms on individuals with PD will be offered to 20 participants of this study, with consent for this data to be recorded and analysed included in the STRIPE consent form.

Participants will be given the option of indicating whether their details can be retained for them to be contacted about potential future research studies that are relevant.

### Interventions

#### Explanation for the choice of comparators {6b}

There is an increasing body of evidence that TTNS can provide meaningful improvement for bladder symptoms in a range of conditions, building on several decades of experience with PTNS. TTNS has the advantage of being non-invasive and simpler to use. The intervention can be used at home and has been demonstrated as non-inferior to PTNS. Where the majority of previous TTNS studies have used TENS machines, we have chosen to use the Geko™ device (Fig. 2) due to the simplicity of use. It is self-adhesive and easy to position on the ankle. It has two buttons and the only variable that can be adjusted is the pulse width (equating to energy of stimulation) using “ + ” and “- “ buttons. These also turn the device on or off if held for a prolonged period. These attributes make it ideal for use in a population with invariable dexterity issues and/or cognitive impairment. Additionally, Geko™ lacks the trailing wires leading to a stimulation unit found in a TENS device which could constitute a trip hazard in a population at risk of gait instability and falls. Geko™ has been approved for use in the UK for the prevention of DVT prophylaxis for the past decade [19], used as a neuromuscular stimulator of the common peroneal nerve to induce leg muscle contraction without mobility. A previous study in idiopathic overactive bladder and multiple sclerosis cohorts has suggested the potential use of the Geko™ device for treating bladder symptoms [18], with a dose–response relationship demonstrated (albeit inverse, assessing weekly versus daily use) suggesting biological effect and potentially a neuronal “coding” effect on bladder function.

